### **General Information**

This document describes the ENCEPH UK Intervention Cluster Randomised Controlled Trial (RCT) and provides information about procedures for entering patients into it. The protocol should not be used as an aide-memoire. Every care was taken in its drafting, but corrections or amendments may be necessary. These will be circulated to the registered investigators in the trial, but centres entering data for the first time are advised to contact the coordinating centre (Brain Infection Group, Liverpool) to confirm they have the most up to date version. Clinical problems relating to this trial should be referred to the relevant Chief Investigator via the relevant study team personnel in the Brain Infections Group.

### **Statement of Compliance**

This study will be carried out in accordance within the Research Governance Framework and follow the International Conference on Harmonisation Good Clinical Practice.

## Glossary

|         |                                                                  |
|---------|------------------------------------------------------------------|
| CI      | Chief Investigator                                               |
| CNS     | Central Nervous System                                           |
| CRF     | Case Report Form                                                 |
| CSF     | Cerebrospinal Fluid                                              |
| CT      | Computer Tomography                                              |
| EEG     | Electroencephalogram                                             |
| HPA     | Health Protection Agency                                         |
| HSV     | Herpes Simplex Virus                                             |
| ICERS   | Incremental Cost-Effectiveness Ratio                             |
| ICH GCP | International Conference on Harmonisation Good Clinical Practice |
| ID      | Identity                                                         |
| ISRCTN  | International Standard Randomised Controlled Trial Number        |
| IV      | Intravenous                                                      |
| LP      | Lumbar Puncture                                                  |
| MREC    | Multi-centre Research Ethics Committee                           |
| MRI     | Magnetic Resonance Imaging                                       |
| N/A     | Not Applicable                                                   |
| N/D     | Not Done                                                         |
| NHS     | National Health Service                                          |
| NIHR    | National Institute of Health Research                            |
| PI      | Principal Investigator                                           |
| PCR     | Polymerase Chain Reaction                                        |
| QALY    | Quality Adjusted Life Year                                       |
| QC      | Quality Control                                                  |
| R&D     | Research & Development                                           |
| RCT     | Randomised Controlled Trial                                      |
| SSA     | Site Specific Assessment                                         |

# 1 PROTOCOL SUMMARY

**Title:** Development and evaluation of an intervention based around the National guidelines on the management of suspected encephalitis, and its evaluation through a cost effectiveness analysis.

**Population:** Secondary care hospitals in the UK will be included. Hospital sites already participating in the ENCEPH-UK study will be excluded so as to reduce the risk of attention bias.

**Number of Sites:** Up to twenty eight secondary care hospitals will be recruited across the UK.

**Study Duration:** Fifteen months per site (to include delivery and evaluation of an intervention at 12 months).

**Description of Intervention:** The intervention will target clinicians (and other healthcare workers) within the hospitals.  
Outcome data will be collected on patients (adults and children) with suspected or confirmed encephalitis.

## **Objectives:**

1. To evaluate the effects of an intervention to improve the clinical management of suspected encephalitis in secondary care.
2. To evaluate the cost-effectiveness of the intervention.

## **Primary outcome**

The proportion of patients with suspected encephalitis\* whose care met all of the following criteria:

- Aciclovir given within 6 hours from admission to hospital at the appropriate dose unless there was an alternative diagnosis; and
- A lumbar puncture (LP) was performed within 12 hours of hospital arrival unless clinically contraindicated.

**The secondary outcomes will be:**

- The proportion of all adults given intra venous (IV) aciclovir for a neurological presentation who met the definition of suspected encephalitis.
- The proportion of all children given IV aciclovir for a neurological presentation who met the definition of suspected encephalitis.
- The proportion of patients with suspected encephalitis who had a lumbar puncture performed within 12 hours unless there was a clinical contraindication.
- The proportion of patients with suspected encephalitis who had a lumbar puncture after resolution of a clinical contraindication to that LP.
- The proportion of patients with suspected encephalitis who had either Magnetic Resonance Imaging (MRI) or Computer Tomography (CT) scan within 24 hours of admission.
- For patients with HSV encephalitis, the proportion who die, have sequelae and appear to make a full recovery upon discharge.
- The proportion of patients with suspected encephalitis having had a lumbar puncture, who had the following CSF investigations performed:
  - CSF:serum glucose ratio calculated
  - HSV PCR performed
- An evaluation of the primary outcomes comparing adults and children enrolled in the RCT.
- A cost effectiveness evaluation of the intervention.

\* Suspected encephalitis is defined as febrile illness or history of a febrile illness with altered behaviours, cognition, personality, or consciousness or new seizures or new focal neurological signs (please see section 5.1 for details).

## Protocol Summary

### Design

Two arm cluster randomised controlled trial comparing a guideline implementation intervention with routine practice.

### Schematic of Study Design:

[figure not shown]

## **2 BACKGROUND INFORMATION**

### **Overview**

This study will evaluate the clinical effectiveness and cost-effectiveness of an intervention to support the implementation of national encephalitis guidelines. Intervention development will be informed by existing evidence on professional behaviour change and sub-studies within the ENCEPH UK programme. The intervention will target clinicians responsible for the diagnosis and initial management of suspected encephalitis. The use of a cluster randomised controlled trial (RCT) in up to twenty eight hospitals with an evaluation period of 12 months will allow both cost effectiveness and clinical outcomes to be assessed.

### **2.1 Introduction**

Encephalitis (inflammation of the brain tissue) is one of the most important types of brain infection because of the devastating impact on those affected. It has a disproportionately large burden on the NHS and community through high health and economic costs, but this has never been quantified. In terms of research, encephalitis is relatively neglected because it is not easily funded from other sources, e.g. major charities.

HSV is the most common viral cause (1) and is treatable with aciclovir, but delays in treatment are associated with poor outcome. There has been little research into how and why delays occur. There are not economic studies in the UK that have attempted to estimate the economic impact of encephalitis. However, settlements for negligent management of a single encephalitis case are around £1-2 million.

### **2.2 Objectives**

It has been found that many patients with suspected encephalitis are started late with aciclovir treatment. The barriers and enablers for the diagnosis and management of encephalitis patients will be assessed as part of a sub-study in the ENCEPH UK programme. This consists of semi structured interviews with health care professionals who have a variety of roles within several hospitals. From this, the major barriers and enablers to using the encephalitis guidelines will be deduced and a novel intervention will be developed and implemented in the hospitals randomised to the intervention arm over twelve months . This intervention will then be assessed for both clinical and cost effectiveness.

### **3 SELECTION OF CENTRES/CLINICIANS**

Study centres will be initiated once all global (e.g. local research and development (R&D) approval) and study specific conditions (e.g. training requirements) have been met, and all necessary documents have been returned to the Brain Infections UK coordinating centre.

All centres will have a consultant and all centres must be equipped with the ability to perform, or have access to, CT/MRI scans and have aseptic conditions for conducting a LP to be performed. Hospitals will be randomised as a unit to either the standard care or intervention arm.

#### **3.1 Centre/Clinician Inclusion Criteria**

- a. Local R&D approval
- b. Completion and return of 'signature and delegation log' to Brain Infections UK
- c. CV and Good Clinical Practice (GCP) certificate to accompany all research personnel recorded on the 'signature and delegation' log
- d. Contractual agreements signed between site and study Sponsor
- e. Receipt of evidence of completion (a) – (e) by Brain Infections UK

#### **3.2 Centre/Clinician Exclusion Criteria**

- a. Not meeting the inclusion criteria listed above
- b. Participating in ENCEPH UK Cohort studies

### **4 TRIAL DESIGN**

A cluster RCT design has been chosen to compare routine practice with an intervention promoting 'best practice' within up to 28 UK hospitals. The intervention taking place in those randomised hospitals will target clinicians. Data on patient care will be collected to assess clinical practice. It is not envisaged that there will be any study related risks to the patients as data collection methods will be similar to the clinical audit that have been performed over the last ten years within our group (2,3). Identifiable data will only be seen by a member of NHS staff currently working at the site and will not be sent to Brain Infections UK. The number of cases, management and cost effectiveness of the intervention will be assessed in all sites.

### **Primary outcome**

The proportion of patients with suspected encephalitis\* whose care met all of the following criteria:

- Aciclovir given within 6 hours of admission to hospital at the appropriate dose unless there was an alternative diagnosis; and
- A LP was performed within 12 hours of hospital arrival unless clinically contraindicated.

### **The secondary outcomes will be:**

- The proportion of all adults given intra venous (IV) aciclovir for a neurological presentation who met the definition of suspected encephalitis.
- The proportion of all children given IV aciclovir for a neurological presentation who met the definition of suspected encephalitis.
- The proportion of patients with suspected encephalitis who had a lumbar puncture performed within 12 hours unless there was a clinical contraindication.
- The proportion of patients with suspected encephalitis who had a lumbar puncture after resolution of a clinical contraindication to that LP.
- The proportion of patients with suspected encephalitis who had either MRI or CT scan within 24 hours of admission.
- For patients with HSV encephalitis, the proportion who die, have sequelae and appear to make a full recovery upon discharge.
- The proportion of patients with suspected encephalitis having had a lumbar puncture, who had the following CSF investigations performed:
  - CSF:serum glucose ratio calculated
  - HSV PCR performed
- An evaluation of the primary outcomes comparing adults and children enrolled in the RCT.
- A cost effectiveness evaluation of the intervention.

*\* Suspected encephalitis is defined as febrile illness or history of a febrile illness with altered behaviours, cognition, personality, or consciousness or new seizures or new focal neurological signs (please see section 5.1 for details).*

There will be a time to event analysis for all of the primary and secondary outcomes listed above within a full time series analysis.

## 5 STUDY POPULATION

### 5.1 Inclusion Criteria

Within this study, any patients who have suspected encephalitis within the twenty eight sites will be included. The inclusion criteria for suspected encephalitis are:

Patients with suspected encephalitis

(a) Mandatory

Acute or sub acute (<4 weeks) alteration in consciousness, cognition, personality or behaviour persisting for more than 24 hours. Personality / behaviour change includes: agitation, psychosis, somnolence, insomnia, catatonia, mood liability, altered sleep pattern and (in children): new onset enuresis, or irritability.

Plus ANY two of:

- Fever ( $> 38^{\circ}\text{C}$ ) / Prodromal illness – acute or sub-acute
- Seizures: New onset
- Focal Neurological Signs – Acute or Sub-acute onset. These include
  - Focal weakness
  - Oromotor dysfunction
  - Movement disorders (chorea, athetosis, dystonia, hemiballisms, stereotypies, orolingual dyskinesia and tics) including Parkinsonism (bradykinesia, tremor, rigidity and postural instability)
  - Amnesia
- Pleocytosis: Cerebrospinal fluid white cell count  $>4$  cells/ $\mu\text{l}$
- Neuroimaging: Compatible with encephalitis
- Electroencephalogram (EEG): compatible with encephalitis

OR

- (b) Clinical suspicion of encephalitis but above investigations have not yet been completed

OR

- (c) Clinical suspicion of encephalitis and the patient died before investigations completed

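### The primary-outcome denominator, suspected encephalitis, is defined in conflicting ways, and section 5.1 can make entry depend on whether a lumbar puncture was done and what it showed

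*Protocol*

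**What the plan says.** Three places in the protocol describe the population of the primary outcome.

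- **Sections 1 and 4, outcome footnote.** Fever or a history of it, with any one of three neurological features: "febrile illness or history of a febrile illness with altered behaviours, cognition, personality, or consciousness or new seizures or new focal neurological signs". There is no minimum duration and no test result. The footnote refers to section 5.1 for details.
- **Section 5.1.** Limb (a) makes altered mental state mandatory: "alteration in consciousness, cognition, personality or behaviour persisting for more than 24 hours". It then asks for more: "Plus ANY two of" six items, namely fever or prodrome, new seizures, focal signs, CSF pleocytosis, compatible imaging and compatible EEG. Limb (b) admits "Clinical suspicion of encephalitis but above investigations have not yet been completed". Limb (c) admits "Clinical suspicion of encephalitis and the patient died before investigations completed".
- **Section 8.2.** The endpoint is stated for patients with suspected CNS infection.

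The primary outcome (sections 1 and 4) requires timely aciclovir and an LP within 12 hours unless contraindicated. Section 6 lists LP practice among the priorities for the intervention. Section 10.3 makes case finding retrospective, uses CSF laboratory records as one of two methods applied at every site, and regards masked data collection as unlikely.

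**The concern.** There are two problems.

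First, the footnote and section 5.1(a) are different rules, and neither contains the other. Abstractors following one or the other would build different denominators. The two secondary outcomes on patients given IV aciclovir (adults and children) are affected as well, because meeting the definition is their numerator.

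Second, under section 5.1 the care being measured can decide who is counted. Pleocytosis counts toward entry under (a), and missing investigations open limb (b). If the intervention changes how often LPs are done, or in whom, it can change the denominator in intervention hospitals after the intervention period. That could bias the comparison between arms and between the two notes reviews, and patients who were never abstracted cannot be recovered in the analysis.

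**Working it through.** **Step 1: do the definitions agree?** Take the 16 combinations of fever, altered state (lasting over 24 hours), new seizure and focal sign, with imaging and EEG not supportive. Compare the footnote with 5.1(a).

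- With no LP result they disagree on 5 of 16. Four meet the footnote only: fever + seizure; fever + focal sign; fever + seizure + focal sign (all three with normal mental state); and fever + altered state alone. One meets 5.1(a) only: altered state + seizure + focal sign without fever.
- With pleocytosis they disagree on 6 of 16: three footnote only (the fever patterns without altered state) and three 5.1(a) only (the afebrile patterns with altered state and at least one of seizure or focal sign).

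**Step 2: where does the LP decide entry?** Take a clinically suspected patient with altered state and exactly one of fever, seizure or focal sign (3 of the 8 altered-state patterns), imaging and EEG not supportive.

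- LP shows pleocytosis: two items, in under (a).
- LP not done: in under (b).
- LP normal: one item, out under (a); out altogether if (b) is read as closed.

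Patients with altered state and two or more clinical features are in under (a) whatever the LP shows.

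**Step 3: the plan's own figure.** Table 2 gives power 0.809 for 20 patients per hospital and 0.05 versus 0.20. Assume two-sided alpha 0.05, 14 hospitals and 6 deaneries per arm, and a normal approximation on the logit scale:

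variance = (1.108² + 1/(20·0.05·0.95))/14 + (1.108² + 1/(20·0.20·0.80))/14 + 2·0.244²/6 = 0.1629 + 0.1100 + 0.0198 = 0.2927

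The true odds ratio is (0.20/0.80)/(0.05/0.95) = 4.75, so z = ln 4.75/√0.2927 − 1.96 = 0.92 and power is 0.82. Table 2 is not in dispute; what is unclear is the population its 0.05 and 0.20 refer to.

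**Step 4: possible size.** The documents give none of the inputs below, so all are assumptions. Let w be the share of suspected patients whose entry turns on the LP, q the chance of pleocytosis if tapped, L the proportion tapped at any time, and c true compliance. Assume an LP closes limb (b) and every compliant patient had an LP. Then

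observed odds = c[1 − w(1−q)] / {(1−c) − w(1−q)(L−c)}

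*Null effect, c = 0.05 in both arms, q equal, L rising.* The observed odds ratio is [0.95 − w(1−q)(L0−0.05)] / [0.95 − w(1−q)(L1−0.05)]. Ranges: w 0.3–0.7, q 0.2–0.5, L0 0.4–0.7, L1 0.8–0.9.

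- Lowest (w 0.3, q 0.5, L 0.7 to 0.8): 0.8525/0.8375 = 1.02
- Mid-range (w 0.5, q 0.35, L 0.55 to 0.85): 0.7875/0.69 = 1.14
- Highest (w 0.7, q 0.2, L 0.4 to 0.9): 0.754/0.474 = 1.59

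With c = 0.05 versus 0.20, the true 4.75 appears as 4·0.8525/0.71 = 4.80 up to 4·0.754/0.408 = 7.39, and as 4·0.7875/0.58875 = 5.35 at mid-range.

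*Compliance taken as equal to LP (L = c).* The last term vanishes and observed odds = [c/(1−c)]·[1 − w(1−q)]. With equal q the odds ratio stays at 4.75. For w 0.1–0.5 and q 0.2–0.6 the observed proportions fall to 0.031–0.048 (control) and 0.130–0.194 (intervention), with power 0.75–0.82 at 20 per hospital. If q is halved in the intervention arm because lower-yield patients are tapped, the odds ratio is 4.75·[1 − w(1−q/2)]/[1 − w(1−q)]: from 4.75·0.91/0.92 = 4.70 (w 0.1, q 0.2) down to 4.75·0.65/0.80 = 3.86 (w 0.5, q 0.6), with power 0.67–0.81.

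**The case against.** The footnote defers to section 5.1, which is headed as the inclusion criteria, so it can be read as a summary with 5.1 as the operative list. Trained staff will use a standardised form. Limbs (b) and (c) need only clinical suspicion, so some patients who meet the footnote but fail (a) would still enter. This narrows the practical mismatch but does not remove it: 5.1 is a different rule rather than an elaboration, and section 8.2 names a third population.

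A reader might infer three stronger things that the text does not support.

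- *That the 24-hour criterion can be known only after the 6-hour and 12-hour windows have closed.* It describes symptom duration, with onset up to four weeks before, and nothing starts the clock at admission. It is a problem only for patients who present within a day of onset.
- *That a normal LP always excludes.* Limb (b) speaks of investigations in the plural. If an outstanding EEG or scan keeps it open, a patient with a normal LP stays in. The protocol does not say, and in a retrospective review the limb has no clear meaning without a time point.
- *That the result will be inflated.* The odds ratio of 1.59 needs one corner of the assumed ranges. At mid-range w and q, a 10-point rise in LP gives about 1.04–1.05. With other assumptions the bias is nil or toward the null.

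**Conclusion.** The conflict between definitions stands on the text alone and needs no assumption. The dependence of entry on LP also stands, but only for patients with altered state and exactly one other clinical feature, without supportive imaging or EEG, and for the normal-LP case only if limb (b) is read as closed.

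Bias between arms and periods is a credible risk, because LP is both an outcome component and an intervention target and abstraction is probably unmasked. It is not a demonstrated effect. The illustrative range for a null effect (1.02 to 1.59) rests wholly on assumed inputs, including that no compliant patient was excused the LP by a contraindication, and the sign changes with how LP practice changes. It should be settled before abstraction because the denominator of the primary outcome depends on it and the change is one of wording.

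**What to change.** State one prevailing definition of suspected encephalitis for the primary-outcome denominator, word for word the same in sections 1, 4, 5.1 and 8.2, and apply it identically in both arms and both notes reviews.

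- The investigators should settle explicitly whether fever is required and how many features are needed, since that is where the texts differ.
- Base entry on features or clinical suspicion documented at presentation, at a fixed time point, so that it does not depend on whether LP, imaging or EEG was done or on the result.
- Treat limbs (b) and (c) the same way, so that clinically suspected but under-investigated patients are kept.
- Keep the investigation-based 5.1(a) set as a sensitivity population.
- Check the 5% control compliance in section 8.3 against the notes review of the 12 months before the intervention, under the chosen definition.

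The cost is protocol and CRF wording before abstraction starts. The downside is that more patients who later prove not to have encephalitis are included, and the 5% may shift, which would require the power table to be looked at again.

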## 5.2 Patient Transfer and Withdrawal

There is a possibility that patients could be transferred to and from the sites within this study. Efforts will be made to establish if any centres regularly receive patient transfers and appropriate recording mechanisms will be put in place. The first 24 hours of a patient's management are the most critical for the primary outcome. Therefore, the patient will be counted at the site of their first admission if initial clinical management takes place within this time period. Should a patient be transferred to a different site within 12 hours, there should still be sufficient data to count the patient within that original study site.

## 6 INTERVENTION DEVELOPMENT AND DELIVERY

Intervention development involves a number of steps, some of which have been undertaken during earlier studies in the programme. These steps comprise:

- Defining priorities for implementation, i.e. key guideline recommendations where there is scope for improved clinical performance;
- Identifying perceived barriers to and enablers of recommended practice;
- Defining candidate intervention components; and
- Constructing a coherent intervention package.

*Defining priorities for implementation.* We already have a good understanding of hospital based performance from studies recently conducted (4, 5), as well as preliminary analysis of the Health Protection Agency (HPA) cohort study. During the ENCEPH-UK programme, we will continue to collect data on the timing of the various diagnostic and treatment decisions.

One priority will be to increase the proportion of patients with suspected encephalitis appropriately and promptly started on treatment with aciclovir. This is chosen because of compelling evidence that not starting treatment for 48 hours or more is associated with a poor outcome in patients with HSV encephalitis.

Other priorities for attention will include the diagnostic tests performed, their sequence and timing, and the grade of clinicians involved in decision making, looking in particular for major deviations away from the guidelines. These are defined as those serious enough to cause appreciable morbidity and mortality (6), and are

based on published guidelines on the management of suspected CNS infections (7-11):

- Performing a LP, without performing imaging first, in a patient with contraindications to an immediate LP (8, 10);
- Delaying a LP in order to perform imaging, when there is no contraindication to an immediate LP (8, 10, 11);
- Failing to perform a diagnostic LP in a patient with a suspected CNS infection, and no contraindications (7, 8, 10, 11); and
- Failure to investigate CSF for cell count, protein, and CSF to plasma glucose ratio when performing a LP.

Priorities for implementation (i.e. key guideline recommendations) will be derived from the Association of British Neurologists and British Infection Association National Guidelines for Management of Suspected Encephalitis in Adults (12) and Paediatrics (13).

*Identifying perceived barriers to and enablers of recommended practice.* Ideally, any intervention to change a given professional behaviour should address factors known to affect that behaviour. For example, if a lack of skills is deterring doctors from performing timely, indicated lumbar punctures, then the intervention could include some form of training in performing lumbar punctures. Often, multiple factors affect professional behaviour and more than one approach may be needed to help change clinical behaviour. For example, lack of confidence (self-efficacy) might also be a factor in deterring doctors from performing indicated lumbar punctures. In that case, some form of clinician mentoring which supports doctors in performing lumbar punctures in relatively easy circumstances or patients until they have mastered the technique in more challenging circumstances or patients might be appropriate.

This work will have been undertaken during the cross sectional interview telephone survey of health care staff undertaken during the Prospective Cohort Study.

*Defining candidate intervention components.* Interventions can be envisaged as having two types of component: a behaviour change technique and a method of delivering that technique. In the above example, a graded task approach is a behaviour change technique, involving the practice of a procedure through increasingly levels of difficulty until it is mastered, which may help doctors in performing lumbar punctures more routinely. The behaviour change technique is

delivered through clinician mentoring. Sometimes, a behaviour change technique can be delivered in more than one way. For example, persuasive communication to increase motivation to perform timely lumbar punctures could be delivered via an interactive educational session or through computerised prompts.

*Constructing a coherent intervention package.* The choice of any given intervention delivery method can be driven by a number of considerations. These include: feasibility (e.g. whether it is possible to adapt local computerised clinical systems to incorporate automated prompts and reminders); acceptability (e.g. to local clinical leaders and their staff); cost (e.g. so that the costs of the intervention do not outweigh the likely benefits); and sustainability (e.g. can the intervention be embedded within continuing systems and routines).

Table 1 illustrates some hypothetical ways in which interventions might be constructed by linking different determinants of behaviour to behaviour change techniques and intervention delivery methods. This phase of development therefore involves judgments about how best to integrate an intervention package which can be delivered to the hospitals randomized to the intervention arm. The intervention will be initially delivered to the intervention hospitals during a four month period and there may be a short reminder every four months to ensure that staff that have newly rotated to that hospital are aware of the intervention if applicable.

